### Plans to promote participant retention and complete follow-up {18b}

Data are collected during routine clinical care assessments.

### Data management {19}

Data are input to a REDCap database by the research nurses. The database is managed by a data management expert affiliated with the provincial health authority. Point of entry data validation mechanisms and systematic data checking algorithms are applied to ensure data quality standards.

### Confidentiality {27}

Numeric participant codes substitute for personal identifiers on research documents. All identifiable participant information is kept in locked cabinets and in password-protected computer files. Confidentiality of participants will be maintained in all forms of results reporting. Participants will be informed in general terms of the results as soon as is practical.

### Plans for collection, laboratory evaluation, and storage of biological specimens for genetic or molecular analysis in this trial/future use {33}

Nasopharyngeal swabs are the only biological specimens collected. These will not be saved.

## Statistical methods

### Statistical methods for primary and secondary outcomes {20a}

#### Descriptive analysis

Means, proportions, and medians will be produced with corresponding measures of variability (standard deviation and interquartile range) for key patient characteristics for the whole population and stratified by treatment assignment, neighborhood clusters, and site. Stage-wise heterogeneity in the descriptive statistics before and after adaption of the new lamps will also be explored. Kaplan–Meier curves will be used to illustrate trends in infection probabilities and a log-rank test will be used to estimate the crude difference in probability of RVI between the treated and control group, stratified by neighborhood clusters and site.

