**Methods:**

Following a study to assay acceptability at each site, this multicenter, double-blinded, cluster-randomized, placebo-controlled trial aims to assess whether far-UVC light devices impact the incidence of RVIs in LTC facilities. Neighborhoods within LTC facilities are randomized to receive far-UVC light devices (222 nm) or identical placebo light devices that emit only visible spectrum light (400–700 nm) in common areas. All residents are monitored for RVIs using both a standard screening protocol and a novel screening protocol that target atypical symptoms. The 3-year incidence of RVIs will be compared using intention-to-treat analysis. A cost-consequence analysis will follow.

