### Trial design {8}

This is a multicenter, double-blinded, cluster randomized, placebo-controlled, superiority trial with two parallel arms. The protocol is registered on ClinicalTrials.gov: registration number NCT05084898. It has pragmatic intent; it aims to inform clinical decisions of whether far-UVC light should be implemented in LTC facilities to reduce the incidence of RVIs. Cluster randomization is necessary because placing far-UVC lights in common areas constitutes a cluster-level intervention.

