**Fig. 1 Fig1:**
[figure not shown]
Trial flow chart

In Phase 1 of the trial, two LTC facilities in Nova Scotia were selected: one in Halifax and one in Falmouth. These locations vary in many aspects, including building type, layout, and size. The layout of the Halifax LTC facility is similar to an acute care ward and has semi-private rooms (private bedroom with shared bathrooms) and shared bedrooms (shared by two residents), whereas the layout of the Falmouth LTC facility is similar to a large house and has private bedrooms and private bathrooms. These sites were selected for the study as a result of feasibility and logistical constraints. There are four participating neighbourhoods at the Halifax LTC facility and two participating neighbourhoods at the Falmouth LTC facility. There are 18–36 residents living in each neighborhood.

In Phase 2, a LTC facility in Cape Breton, Nova Scotia, was added to the trial. It has private bedrooms with private bathrooms and semi-private rooms. There are five participating neighborhoods in this LTC facility.

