### Criteria for discontinuing or modifying allocated interventions {11b}

Far-UVC light in common areas is a cluster-level intervention. Therefore, it is infeasible to modify it for an individual participant. Based on previous studies, it is anticipated to pose minimal risk to participants.

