## Assignment of interventions: allocation

### Sequence generation {16a}

Randomization is at the level of “neighborhoods” within LTC facilities (distinct areas within LTC facilities that house social groups of 18–36 residents). In Phase 1, neighborhoods in the Halifax and Falmouth LTC facilities, 16 in total, were randomized with a 1:1 allocation ratio. In Phase 2, five neighborhoods were randomized in the Cape Breton LTC facility: two to the placebo arm and three to the active arm. Randomization is stratified by LTC facility. Randomization was performed by a blinded biostatistician who is otherwise uninvolved with the study using SAS 9.4 software. 

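### The crude log-rank test is stratified by neighborhood, the unit that was randomized, so it cannot be computed as written; site is the stratum it needs

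*Protocol article*

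**What the plan says.** The sentence at issue closes the Descriptive analysis paragraph of Statistical methods {20a} in the protocol article. It pairs Kaplan–Meier curves with a log-rank test, and the test is to address the "crude difference in probability of RVI between the treated and control group, stratified by neighborhood clusters and site".

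The design is stated consistently elsewhere in the article:

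- Sequence generation {16a}: "Randomization is at the level of “neighborhoods” within LTC facilities", and "Randomization is stratified by LTC facility".
- Abstract, Methods: "Neighborhoods within LTC facilities are randomized to receive far-UVC light devices (222 nm) or identical placebo light devices".
- Trial design {8}: "Cluster randomization is necessary because placing far-UVC lights in common areas constitutes a cluster-level intervention".
- Criteria for discontinuing or modifying allocated interventions {11b}, on the cluster-level lamps: "Therefore, it is infeasible to modify it for an individual participant".

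The Primary analysis section handles neighborhood and site differently. It uses a Cox model with mixed effects for the clustering.

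**The concern.** A stratified log-rank test compares the arms within each stratum and adds up the results. It therefore needs strata in which both arms are present. Here one of the two named stratification factors is the randomized unit itself, and no neighborhood has both arms. Stratifying on that unit does not adjust for within-neighborhood correlation; it removes the treatment contrast.

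What is at stake is the only crude between-arm test of RVI that the article describes. An analyst following the text will get an error or an empty statistic, and will then have to choose a replacement after the data are in. Several replacements are possible (site strata, no strata, a cluster-adjusted version) and they can give different p-values. The choice is better made now.

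**Working it through.** **1. Which test the sample size uses.** The only log-rank figures in the article are the totals in Sample size {14}: 470 and 968 participants, without the ICC, for control survival of 0.4 and 0.7. Inputs: hazard ratio 0.7, power 0.8, alpha 0.05 (taken as two-sided; the article does not say).

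- Freedman events: (1.960 + 0.842)² × ((1 + 0.7)/(1 − 0.7))² = 7.849 × 32.11 ≈ 252.0.
- Participants: events / [1 − (S + S^0.7)/2].
- S = 0.4: S^0.7 = 0.527, mean event probability 0.537, total 469.6, so 470.
- S = 0.7: S^0.7 = 0.779, mean event probability 0.260, total 967.6, so 968.

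Both figures reproduce from the ordinary formula with no strata. The sizing test is therefore not the neighborhood-stratified test.

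**2. The algebra of the planned test.** In a stratum, at an event time with d events, n at risk and n₁ of those in the active arm:

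- observed minus expected: d₁ − d·n₁/n
- variance: d·(n₁/n)·(1 − n₁/n)·(n − d)/(n − 1)

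In an active neighborhood n₁ = n and d₁ = d, so the first line is d − d = 0 and the second contains the factor 1 − 1 = 0. In a placebo neighborhood n₁ = 0 and d₁ = 0, so both lines are 0. Every term vanishes. The sums are U = 0 and V = 0, and the chi-square U²/V is 0/0. Crossing neighborhood with site gives the same strata again, because each neighborhood lies in one site.

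**3. Check by simulation.** Assumptions: 11 neighborhoods split 2/2 (Halifax), 1/1 (Falmouth), and 3 active/2 placebo (Cape Breton); 45 residents in each (about 500/11); control incidence 0.22 per person-year; censoring uniform between 0.2 and 3 years; no within-neighborhood correlation. The Cape Breton split is stated in the article. The other two are inferred from 1:1 allocation stratified by facility. One trial was drawn per hazard ratio.

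| True HR | Events | Neighborhood strata, alone or with site: U, V | Site strata: U, V | Site-strata chi-square (U²/V) |
|---|---|---|---|---|
| 1 | 140 | 0, 0 | −7.3, 34.1 | 1.6 |
| 0.7 | 111 | 0, 0 | −13.9, 27.0 | 7.2 |
| 0.1 | 82 | 0, 0 | −39.9, 19.9 | 80.0 |

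Standard software stopped with a singular-matrix error for the neighborhood strata and returned a result for the site strata. The site-strata values illustrate only that the test is then defined. They make no allowance for clustering and do not forecast this trial's result. The zeros in the third column need none of the simulation assumptions.

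**4. Why dropping the strata is not a free repair.** With the article's ICC of 0.12 and 20–25 participants per cluster, the approximate design effect 1 + (m − 1)·ICC runs from 1 + 19 × 0.12 = 3.28 to 1 + 24 × 0.12 = 3.88. The article calls this ICC unreliable. Over its interval of 0.002 to 0.883 the design effect runs from 1 + 19 × 0.002 = 1.04 to 1 + 24 × 0.883 = 22.2. Clustering cannot be assumed negligible in a crude p-value.

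**The case against.** The best defense is that the word stratified is used loosely. Earlier in the same paragraph it means tabulated by, and the closing phrase could be meant for the Kaplan–Meier curves, which can be drawn for each neighborhood. That is a fair guess at intent, but it does not rescue the test. The phrase is attached to the treated-versus-control comparison, and a separate comparison inside each neighborhood also has no comparator. Residents who move, if stratified by current neighborhood but analyzed by original arm, could in theory produce a mixed stratum. The article describes no such analysis.

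The second defense is about consequence, and it stands. The test is labeled crude and sits under a descriptive heading. The trial's conclusion comes from the mixed-effects Cox model, in which neighborhood enters as a clustering effect; that model is not made undefined by this sentence. The failure also announces itself, so no wrong number can come from the test as written.

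Two stronger readings are tempting and unsupported. A reader might infer that the sample size rests on an impossible test, since it too is a log-rank calculation. But Sample size {14} describes a log-rank test for a cluster design without neighborhood strata, and its figures reproduce from the unstratified formula. A reader might also infer that the trial will report a p-value that ignores clustering. The article does not say that the strata would be dropped, and its treatment of clustering elsewhere shows that the authors are aware of the issue. It is a risk of leaving the sentence uncorrected, not something the plan states.

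**Conclusion.** The point holds for the crude log-rank test. As written, it has zero numerator and zero variance for any data, and it cannot be computed. This follows from one fact, stated repeatedly in the article: each neighborhood receives one arm. It does not depend on the number of neighborhoods, the event rate or the true effect.

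It is a moderate correction to a secondary, descriptive test. This is an error in what the article states, not a detail left to the full protocol or analysis plan, because the test, the contrast and the strata are all named.

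**What to change.** In the Descriptive analysis sentence, remove neighborhood from the log-rank strata and stratify by site only, in line with the randomization. Then choose one of these and say so:

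- **Re-randomization p-value.** Re-allocate neighborhoods within site and compare the observed site-stratified statistic with the resulting distribution. With 4, 2 and 5 neighborhoods split 2/2, 1/1 and 3/2, there are C(4,2) × C(2,1) × C(5,3) = 6 × 2 × 10 = 120 allocations, so the smallest attainable p-value is 1/120 ≈ 0.008. The 120 is conditional. Study setting {9} says "There are four participating neighbourhoods at the Halifax LTC facility and two participating neighbourhoods at the Falmouth LTC facility", and Sequence generation {16a} says "five neighborhoods were randomized in the Cape Breton LTC facility: two to the placebo arm and three to the active arm", but that same section gives a Phase 1 total of 16 neighborhoods, against 4 + 2 = 6. The counts must be reconciled before the allocation set is fixed.
- **Cluster-adjusted log-rank test**, stratified by site.
- **No p-value.** Present the crude comparison as descriptive and leave inference to the mixed-effects Cox model.

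Keep Kaplan–Meier curves by neighborhood for display only.

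The cost is one sentence of wording and a few lines of code. A p-value that allows for clustering will generally be less favorable than one from a naive unstratified test.

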#### Primary analysis

The primary analysis will be an intention-to-treat effect estimated via comparison of 3-year incidence of COVID-19 or RVIs among individuals assigned to each treatment group. We will use a Cox model, which has the flexibility to account for the clustered nature of the data and adjust for prognostic factors, to estimate the hazard ratio. We will account for clustering within neighborhoods and by site using mixed-effects models [43]. Prognostic factors, at the individual (i.e., age, sex and frailty) will be explored and potentially adjusted for [44]. It is recommended that cluster-level prognostic factors are also adjusted for incluster randomized trials; however, we do not anticipate much variation here.

The change in lamps in Phase 2 present some unique analytical challenges. Participants in Phase 2 will presumably experience higher levels of far-UVC exposure. We will explore whether infection rates change between the two phases and will likely add a binary indicator to divide the person-time contributed into Phase 1 and Phase 2.

#### Person-time in study

Time zero will be defined by the date the lamps are turned on for all those enrolled at the beginning of the trial. For those enrolled subsequently, time zero is the date of consent. The person is followed until they are diagnosed with COVID-19 or other RVI, die, the study concludes, or participant withdrawal (administrative censoring). If a participant leaves the LTC facility for more than 24 h (e.g., is hospitalized), that person-time is excluded from the analysis. Participants who leave the LTC facilities may have an increased risk of infection. We will perform a sensitivity analysis where we introduce a washout period for all infections contracted 2 weeks after an absence from the home of more than 24 hours.

#### Secondary analysis

To assess the inter-rater reliability of the novel RVI screening protocol, prior to the trial, two research nurses assessed every participant once every 7 days, and concordance between raters was tracked. We will explore inter-rater agreement of each component (SQiD, SQiF, SQiRM, 4AT, and HABAM) using several agreement coefficients and their 95% confidence intervals, including percent agreement, kappa, Fliess’s kappa, Gwet’s AC, and Krippendorff’s alpha coefficient. Analysis will be carried out using Stata package *kappaetc* which follows methods and formulas discussed in Gwet [45]. We will also look at the sum of scores for SQiD, SQiF, and SQiRM and determine agreement for the overall score using the above measure and possibly ICC using a two-way mixed-effects model, provided model assumptions are met.

To assess the validity of the novel RVI screening protocol, the sensitivity, specificity, positive predictive value, and negative predictive value will be compared to the standard RVI screening protocol. Additionally, concordance between answers on the SQiD, SQirM, SQiF, 4AT, and HABAM will be tracked to determine if any questions are capturing otherwise undetected information.

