### Sample size {14}

Prior to Phase 1, sample size estimations were limited by uncertainty surrounding the expected incidence of SARS-CoV-2 in the study setting. The approach taken here was to include as many clusters as feasibly possible given budget and logistical constraints, and then estimate the necessary sample size 1 year into the study.

The sample size was determined using a log-rank test comparing two survival rates in a cluster randomized design. The intra-class correlation coefficient (ICC) for the neighborhoods and the survival probability for the entire sample was calculated using the data collected by year 1. The survival probability should be calculated for just the control group; however, using the entire sample enabled the primary biostatistician to remain blinded, which is the recommended practice [29–31]. Theoretically, this approach would lead us to overestimate the necessary sample (if we assume the treated group had less or equal cases to the control group).

At the time of the interim analysis, there were 178 participants in the trial (20–25 per cluster), and the median time in the study was 0.98 years (*IQR*: 0.49–1.02). There were 30 cases resulting in an incidence rate of 0.22 (95% *CI*: 0.15–0.31). The ICC was estimated using a random effects logistic regression model [32], but the low incidence rate meant the estimate was not reliable (*ICC* = 0.12, 95% *CI*: 0.002–0.883). We believe that our incidence rate estimate of 0.22 cases per year is low and unlikely to represent the future rates of infection because of the changes in prevention strategies since the first year of data collection. We have therefore modelled several scenarios where we vary the survival probability between 0.4 and 0.7 (Additional File 1).

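### Two nurses rated the same residents weekly, but the agreement intervals have no stated provision for the repeats; pooled as independent pairs, they would be too narrow

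*Protocol article*

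**What the plan says.** The Protocol article, Statistical methods {20a}, Secondary analysis, places the reliability work before the trial: "To assess the inter-rater reliability of the novel RVI screening protocol, prior to the trial", it says, "two research nurses assessed every participant once every 7 days, and concordance between raters was tracked". The components rated are SQiD, SQiF, SQiRM, 4AT and HABAM.

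Agreement on each component is to be explored "using several agreement coefficients and their 95% confidence intervals, including percent agreement, kappa, Fliess’s kappa, Gwet’s AC, and Krippendorff’s alpha coefficient". The software is the Stata package kappaetc, with one cited text for its formulas. For the sum of the three single-question scores the plan adds "possibly ICC using a two-way mixed-effects model, provided model assumptions are met".

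The section does not state the number of weeks rated, whether the weeks are pooled, or whether the unit behind each interval is the resident or the resident-week. Clustering is addressed under Primary analysis, for the Cox model only: "We will account for clustering within neighborhoods and by site using mixed-effects models". That sentence concerns neighborhoods and sites, not repeated ratings of one resident.

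**The concern.** Residents are sampled once but measured repeatedly. Some are likely to be harder to rate than others. The article says that dementia and frailty are highly prevalent in these facilities, and it records whether a resident is verbal. A resident on whom the nurses disagree one week may well produce disagreement the next. Ten weekly pairs on one resident then carry less information than ten pairs on ten residents.

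The methods are named in some detail, but none comes with a resident-level cluster, a resampling unit or a week term. A two-way ICC has a subject factor and a rater factor. If all weeks are used with nothing added, each resident-week becomes a subject.

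What is at stake is the stated precision of agreement. SQiRM and SQiF are assessed for the first time here, and SQiD has not been validated in long-term care. Readers deciding whether to adopt these tools will look at the lower limits of the intervals. Under pooling, each further week on the same residents would increase the false precision.

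**Working it through.** The plan gives no figure for this analysis (no number of pairs, expected kappa or interval width), so there is nothing to reproduce. The check asks what pooling would do.

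**Inputs.** From Secondary analysis: two raters, every participant, one pair per resident per week. Assumed: m weekly pairs per resident, and rho, the within-resident correlation of a pair's contribution to the coefficient.

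**Design effect.** With m pairs per resident, the variance is multiplied by DE = 1 + (m − 1) × rho. The correct interval is √DE times as wide as the pooled one. Actual coverage of the pooled nominal 95% interval is 2Φ(1.96/√DE) − 1.

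| m (weeks) | rho | DE | √DE | Actual coverage |
|---|---|---|---|---|
| 1 | any | 1 | 1.00 | 95% |
| any | 0 | 1 | 1.00 | 95% |
| 4 | 0.1 | 1 + 3 × 0.1 = 1.3 | 1.14 | 91% |
| 8 | 0.2 | 1 + 7 × 0.2 = 2.4 | 1.55 | 79% |
| 12 | 0.3 | 1 + 11 × 0.3 = 4.3 | 2.07 | 66% |

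The number of residents does not enter this formula.

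**Simulation.** A binary item was rated by two raters on 178 residents, with 1,500 runs per setting. A jackknife over pairs was compared with a jackknife over residents, for percent agreement, kappa and Gwet's AC1. The number rated before the trial is not given. The figure 178 is a stand-in taken from Sample size {14}, which reports that at year 1 "there were 178 participants in the trial (20–25 per cluster").

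- *Trait and rater error both vary moderately between residents.* Pair-level coverage was about 91–92% at 4 weeks, 87–88% at 8 and 82–84% at 12. Standard errors were too small by factors of 1.11–1.14, 1.24–1.30 and 1.36–1.44.
- *Both vary more strongly.* Pair-level coverage was about 90%, 81–82% and 74–77%.
- *Resident-level jackknife, in both settings at 4 to 12 weeks.* Coverage stayed at 94–96%.
- *Only the trait varies between residents, not rater error.* Percent agreement and AC1 were almost unaffected (standard-error ratio 1.00–1.02). Kappa's standard error was too small by 1.04–1.13.
- *No variation between residents, or one pair per resident.* The two jackknives gave the same standard errors.

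The direction therefore follows from the stated design once pairs are pooled and agreement is correlated within residents. The size depends on figures that the article does not give.

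**The case against.** The strongest reply is that the article never says each rating pair is treated as an independent subject. A reader might infer this from the coefficients and the package, and conclude that the intervals will be too narrow. The text does not support that step. One pair per resident, a week-by-week analysis, or clustered or resampled intervals would all fit what is written. Whether kappaetc can handle clustering cannot be settled from the article, which prints no variance formula. This reply stands, and it makes the point conditional.

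It can also be said that a condensed article may leave the unit of an exploratory agreement analysis to the full protocol or analysis plan, neither of which is shown. That limits the weight of the point. It does not remove it, because the article goes as far as naming the coefficients, intervals, package and ICC model alongside a repeated design, and what it names has no visible place for the repeats.

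The ICC is only a possibility and depends on its assumptions being met. Independence of the rated units is one of those assumptions, so the article does not commit to fitting it on dependent rows.

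Finally, the plan sets no reliability threshold or decision rule, and Outcomes {12} does not list inter-rater agreement by name. A reader might infer that the trial could wrongly declare a tool reliable, but the article defines no such declaration. Severe figures, such as about 56% coverage at 12 weeks with rho 0.5, are arithmetically right, but nothing in the article supports those inputs.

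**Conclusion.** The point holds conditionally and is minor. The stated data are repeated on residents, and the stated agreement analysis makes no provision for it. The intervals would be too narrow if two things are true: weekly pairs are pooled as independent, and agreement is correlated within residents. Under the assumed values in the table, nominal 95% coverage falls to between about 91% and 66%. It does not fall at all with one pair per resident or zero correlation. If residents differ only in the trait and not in how reliably they are rated, percent agreement and AC1 lose almost nothing and kappa a little. The point estimates of agreement and the primary Cox analysis are untouched.

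**What to change.** State the unit of analysis and how many weeks are used. Keep the named coefficients, but take their 95% intervals from a bootstrap or jackknife that resamples whole residents, with all of a resident's weeks kept together. Alternatively, use one rating pair per resident, such as the first. If the sum-score ICC is fitted on all weeks, add a resident-by-week random term to the resident and rater terms.

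The ratings were collected before the trial, so no new data are needed: the cost is a sentence of analysis wording and a few lines of code. The downside is wider, less favourable reliability intervals. Using one pair per resident also discards the remaining weeks.
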